### Statistical methods

All data analyses will be carried out according to a pre-established analysis plan. The main null-hypothesis to be tested is that there is no difference between the two intervention arms with regard to the plasma cortisol AUC-total in the DEX-CRH test. All randomized participants will be analysed, including those with missing data on AUC.

Statistical analyses will be performed using ANCOVA [65]. Thus, the outcomes will be analysed as the difference for the individual participant's before and after the intervention, firstly unadjusted and then adjusted for a number of variables, if they present with a p-value < 0.1 in the univariate analyses [66], see Table 1. Initially the drug level measured in each participant will not be included in the models in order as to keep the analysers blinded. Later on analyses for the effect of drug-level will be performed along with other significant covariates in the multivariate model. Separate analyses will be performed in a log linear model of the changes in the primary outcome as compared to the secondary and tertiary outcomes.

**Table 1 T1:** Covariates in the statistical models for the AGENDA trial.

Outcome	Primary outcome: AUC-total plasma cortisol	Secondary outcome Neuroticism	Secondary outcome Cognitive function	Tertiary outcomes
AUC-total plasma cortisol	x	x		x

Age	x	x	x	x

Gender	x	x	x	x

HAMD, entry	x		x	x

Body Mass Index, entry	x			

Number of daily cigarettes	x			

Danish Adult Reading Test			x	

Years of education		x		

Drug-level	x	x	x	x

In the case of missing data according to the primary outcome, analyses will be performed both on complete data sets, as well as data sets on all participants completed by multiple imputation (MI) of missing data by MI-analysis (SASS version 9.1 or NORM version 1) based on age, sex, body mass index, HAMD, neuroticism before and after the intervention, years of education, and AUC-total for cortisol, and ACTH and salivary cortisol before and after the intervention. In the case of discrepancy between these results, the result from the MI procedure is regarded as the result in the trial. P < 0.05 will be regarded as statistically significant.

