### Sample size

A high-risk study performed by Modell et al. [9] found that healthy high-risk probands of patients with a diagnosis of depression examined by the DEX-CRH test present with a cortisol AUC-total (mean ± SEM) of 15,064 ± 3,947 nmol × min/L. Further, Modell et al reported that cortisol AUC-total (mean ± SEM) in healthy individuals with no family history of depression was 7,773 ± 1,071 nmol × min/L. A clinically relevant effect of escitalopram on the cortisol AUC-total (mean ± SEM) was thus estimated to be the difference in cortisol AUC-total (mean ± SEM) of high-risk probands of patients with the diagnosis of depression and that of healthy individuals with no family history of depression. Accordingly, the relevant difference we aim to detect or reject is 15,064 – 7,773 = 7,291 nmol × min/L. Given a standard deviation (SD) = SEM × √14 = 3,947 × 3.7 = 14,768 nmol × min/L provides a power of the trial at a minimum of 60% (1 - β = 0.60), β being the risk of overlooking a difference in the cortisol AUC-total. However, the power in the trial may be higher, considering the use of analysis of covariance (ANCOVA) of the change from entry to after four weeks of intervention in AUC total during the DEX-CRH test. Based on these calculations we aim for a full data set of 80 participants to be able to conclude in relation to the primary outcome measure.

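### Cortisol AUC-total is strongly skewed on the plan's own figures, yet it is analysed first as an unadjusted change, with entry AUC screened and no scale fixed for analysis or imputation

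*Protocol article*

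**What the plan says.** Under Statistical methods, the Protocol article names ANCOVA and says that "the outcomes will be analysed as the difference for the individual participant's before and after the intervention". The differences are analysed first unadjusted, then adjusted for those Table 1 variables that reach p < 0.1 in univariate analysis. Table 1 lists AUC-total plasma cortisol, age and gender among the covariates for the primary outcome. The text does not say which of the two analyses decides. A log linear model appears only for separate analyses relating changes in the primary outcome to the other outcomes, not for the comparison of arms.

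Missing primary data are to be multiply imputed in one of two named packages, with cortisol, ACTH and salivary cortisol AUCs among the variables. No transformation or bound is named. If complete-case and imputed results differ, the imputed result stands.

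The Sample size section describes relatives who "present with a cortisol AUC-total (mean ± SEM) of 15,064 ± 3,947 nmol × min/L" and derives the SD as "SEM × √14 = 3,947 × 3.7 = 14,768 nmol × min/L". The target is on the raw scale: "the relevant difference we aim to detect or reject is 15,064 – 7,773 = 7,291 nmol × min/L".

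**The concern.** An SD about as large as the mean, in a quantity that cannot be negative, means a long right tail. Two consequences follow for the primary comparison.

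First, an unadjusted raw difference carries the variance of two skewed measurements, so a few high secretors can dominate it. Entry AUC is the obvious covariate to remove much of that noise, but the plan leaves it out of the first analysis and admits it to the second only through a p-value screen. The stratification factors, age and sex, face the same screen. In a trial that plans for only 60% power, this matters.

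Second, the imputation can override the complete-case result. A normal imputation model fitted to untransformed AUC can produce values that no participant could have.

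**Working it through.** **Inputs (Protocol article).** From Sample size: high-risk mean 15,064, SEM 3,947, n = 14 implied by the √14; no-family-history group "in healthy individuals with no family history of depression was 7,773 ± 1,071 nmol × min/L", group size not given; difference 7,291; 80 participants. From Randomization: 1:1 allocation. From Statistical methods: significance level 0.05, taken as two-sided.

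**Reproducing the plan's power.** SD = 3,947 × √14 = 14,768. Standard error of the difference = 14,768 × √(2/40) = 3,302. Then 7,291/3,302 = 2.208, and Φ(2.208 − 1.96) = 59.8%. The stated 60% is right for these inputs.

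**Skewness.** CV = 14,768/15,064 = 0.98. A normal distribution with this mean and SD has Φ(−15,064/14,768) = 15.4% of its mass below zero, so it cannot describe an AUC of a concentration.

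**Power by analysis (simulated, 40 per arm).** Assumptions: lognormal AUC with log-SD = √ln(1 + 0.98²) = 0.82, the same CV in both arms, and a proportional effect of 7,773/15,064 = 0.516. The before-after correlation is not in the article, so a range is shown.

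| Log-scale correlation | Raw change, unadjusted | Raw ANCOVA | Log ANCOVA |
|---|---|---|---|
| 0.3 | 53% | 87% | 95% |
| 0.5 | 64% | 91% | 99% |
| 0.7 | 80% | 97% | nearly 100% |

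Simulation error is about one point. Moving from raw change to raw ANCOVA gains about 16 to 33 points; moving from raw to log ANCOVA gains about 3 to 9. For a smaller effect, a 25% reduction, the three figures are 21%, 32% and 42% at correlation 0.5, and 31%, 42% and 59% at 0.7.

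**Does the log advantage depend on the assumed effect?** Yes.
- The no-family-history group's CV is 1,071 × √n / 7,773: 44% for n = 10, 52% for n = 14 and 75% for n = 30 (n assumed).
- If the treated arm takes that group's mean and a CV of 52%, at correlation 0.5, raw ANCOVA has 98% and log ANCOVA about 90%. At a CV of 75% they are about equal (95% and 97%).
- If treatment removes 70% of each value's excess above 7,773, raw ANCOVA has about 81% and log ANCOVA 56%.
- In every setting with a true effect, both ANCOVAs beat the unadjusted raw change.

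**Ratio of geometric means.** Under lognormality it equals 0.516 × √[(1 + 0.98²)/(1 + CV²)], where CV is that of the no-family-history group. This gives 0.66, 0.64 and 0.58 for n = 10, 14 and 30. It equals 0.52 only if the two CVs are equal.

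**Imputation.** In the same lognormal simulations, a normal model for four-week AUC given arm and entry AUC put 13 to 16% of its predictive draws below zero, about one in seven.

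**The case against.** Four points on the other side carry weight.

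- **The article does plan ANCOVA.** Sample size notes that it may raise power above 60%, and Table 1 lists AUC-total. The screen would also usually admit entry AUC. With equal variances and correlation ρ, change correlates with entry at −√((1 − ρ)/2), which is −0.50 at ρ = 0.5 and −0.39 at ρ = 0.7. With 80 participants the t statistic, |r|√78/√(1 − r²), is about 5.1 and 3.7. This stands and narrows the point. The weakness is that an unadjusted change comes first, that the text does not say which analysis decides, and that a covariate known to matter depends on a screen at all.
- **A reader might infer that AUC is imputed on the raw scale and that negative values will occur.** The documents do not support that. The scale is not stated, the article condenses a fuller protocol, and the pre-established analysis plan is not shown. A transformation may be specified there.
- **A reader might infer that the raw scale itself costs much power.** It does not at the planned effect once entry AUC is included, and the sign of the difference depends on how the drug acts.
- **No invalidity is shown.** Type I error stayed at 4 to 5% for all three analyses. No bias from imputation was demonstrated either. Of 77 randomized, 64 were complete in May 2009, but some of the other 13 may still have been in treatment. Even if all 13 were missing, one draw in seven is about two negative values per imputed data set.

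The 98% CV also rests on an implied 14 people in one earlier study, and a few extreme values could have inflated it.

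**Conclusion.** The point holds as one of efficiency and pre-specification. The skewness follows directly from the plan's figures. The unadjusted raw change is the weakest of the analyses compared: about 53 to 81% power, against about 87 to 97% for raw ANCOVA that always includes entry AUC. These figures assume a lognormal AUC, a proportional effect and log-scale correlations of 0.3 to 0.7.

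The case for logs over raw units is weaker. It is worth about 3 to 9 points under a proportional effect with equal CVs, and it reverses under other plausible effects. Impossible imputed values are a conditional risk: they arise only if AUC is left untransformed and unbounded in a normal model. The 60% power statement is not an arithmetic error.

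**What to change.** Before code break:

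- Make the primary analysis an ANCOVA of four-week AUC-total on arm, always including entry AUC-total, age stratum and sex, with no p < 0.1 screening.
- Fix the scale in advance. The suggestion is log, reporting the ratio of geometric means with a 95% confidence interval, with raw-scale ANCOVA and the raw difference as a sensitivity analysis.
- State the imputation scale, and impute the skewed hormone AUCs (cortisol, ACTH, salivary cortisol) on the log scale.
- Do not give 0.52 as the geometric-mean target unless equal CVs are assumed. With the no-family-history SEM and an assumed group size of 10 to 30, it is about 0.58 to 0.66.

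The cost is wording in the analysis plan. Participants, measurements and sample size do not change. The downside is that the effect is reported as a ratio, the planned raw difference of 7,291 becomes secondary, and the log scale would lose power if the drug mainly lowers high values. That last risk is why the raw-scale ANCOVA should be kept and named in advance.

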### Randomization

Randomization into one of the two intervention groups is done immediately after it has been established that the participant fulfils all the inclusion criteria and none of the exclusion criteria. Randomization is stratified by age (18 – 31 years and 32 – 60 years) and sex in order to get an equal distribution in the intervention groups, knowing that the response to the DEX-CRH test is sensitive to these factors. Participants are randomized in a 1-to-1 ratio to receive escitalopram 10 mg or placebo. The Copenhagen Trial Unit (CTU), Centre for Clinical Intervention Research, Rigshospitalet performs the centralised randomization, and only the IT Manager of the CTU will know the block size used for stratification. The sponsor-investigator (UK) provides information of the participants to the CTU during the entry assessment as soon as participation in the study has been decided. CTU performs the computer-generated randomization to ensure adequate allocation concealment and adequate generation of the allocation sequence [35]. The number of the allocated treatment is communicated to UK, both by phone and email.

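### The primary outcome gets an unadjusted change-score analysis and one adjusted by a p<0.1 screen that spares neither entry AUC-total nor the stratification factors, and the protocol does not say which decides

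*Protocol article*

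**What the plan says.** The Statistical methods section names ANCOVA as the method and defines each outcome as the individual before-after difference, analysed "firstly unadjusted and then adjusted for a number of variables, if they present with a p-value < 0.1 in the univariate analyses". For the primary outcome, Table 1 lists as candidates AUC-total plasma cortisol, age, gender, entry HAMD, entry body mass index, daily cigarettes and drug level (the last held back at first to protect blinding). No candidate is exempted from the screen. The same section sets the threshold: "P < 0.05 will be regarded as statistically significant". It has a precedence rule for missing data, under which multiple imputation (MI) overrides the complete-case result, but none for unadjusted against adjusted results.

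The Randomization section stratifies by age (18–31, 32–60) and sex, "knowing that the response to the DEX-CRH test is sensitive to these factors".

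The Sample size section bases its power figure on a between-group difference and a single-occasion SD, then adds that "the power in the trial may be higher, considering the use of analysis of covariance (ANCOVA) of the change".

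**The concern.** Three features of the stated rule are unsatisfactory.

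- **Two results for one hypothesis.** The protocol asks for both an unadjusted and an adjusted test of the primary outcome and does not designate one. The content of the second is set by the trial's own data.
- **Strata subject to screening.** Age and sex were built into the randomization because they were believed to affect the response, yet each enters the model only if its univariate p-value is below 0.1. When randomization is balanced within strata and the model leaves them out, the standard error is usually too large.
- **Unadjusted change is the less efficient analysis.** Subtracting the entry value is not the same as adjusting for it. For any correlation below 1 the unadjusted change score is less precise than ANCOVA with the entry value as covariate. In a trial planned at 60% power there is little to spare.

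**Working it through.** **Inputs.** The difference comes from the Sample size section: "the relevant difference we aim to detect or reject is 15,064 – 7,773 = 7,291 nmol × min/L". So does the SD: "Given a standard deviation (SD) = SEM × √14 = 3,947 × 3.7 = 14,768 nmol × min/L". This is an SD of AUC-total at one visit, not of its change. The total is 80, allocated 1:1, so 40 per arm. Alpha is 0.05, taken as two-sided because the article does not state sidedness. The correlation ρ between entry and week-4 AUC-total is not given, so it is an assumption, shown at 0.3, 0.5 and 0.7.

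**Step 1: the plan's own figure.** The standard error is 14,768 × √(2/40) = 3,302, and 7,291 / 3,302 = 2.208. Power is 59.8% by the normal approximation and 58.7% by the noncentral t. The article says the sample size "provides a power of the trial at a minimum of 60% (1 - β = 0.60". The figure reproduces.

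**Step 2: unadjusted change against baseline-adjusted ANCOVA.** With equal SD at both visits:

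- SD of change = SD × √(2(1 − ρ))
- residual SD of ANCOVA = SD × √(1 − ρ²)
- variance ratio, ANCOVA to change = (1 + ρ)/2

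Noncentral-t power, 40 per arm:

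| ρ (assumed) | SD of change | Power, change | Residual SD, ANCOVA | Power, ANCOVA |
|---|---|---|---|---|
| 0.3 | 17,474 | 45% | 14,088 | 63% |
| 0.5 | 14,768 | 59% | 12,789 | 71% |
| 0.7 | 11,439 | 80% | 10,546 | 86% |

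At ρ = 0.5 the SD of change equals the single-visit SD, because √(2 × 0.5) = 1. The stated 60% is therefore the power of an unadjusted change score only at about that correlation. Below it, power falls under the stated minimum. At ρ = 0 the ANCOVA residual SD equals the single-visit SD, so ANCOVA starts from the stated figure and only gains.

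**Step 3: the screened model.** A simulation of 80 participants (4,000 replicates, exact balance within strata) let age group, sex and three other covariates shift AUC-total equally at both visits, with small assumed effects. It read the AUC-total row of Table 1 as the entry value. Power under the target difference:

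| ρ | Unadjusted change | p<0.1 screened | ANCOVA on entry AUC-total, age group, sex | Unadjusted and screened disagree on significance |
|---|---|---|---|---|
| 0.3 | 44% | 62% | 64% | 24% of trials |
| 0.5 | 58% | 69% | 71% | 18% |
| 0.7 | 79% | 85% | 86% | 10% |

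Entry AUC-total passed the screen in 96 to 100% of trials, so the screened model keeps nearly all of the ANCOVA gain. Age and sex each passed in only about 8 to 10%. A factor that shifts the level but not the change has no univariate association with the change, so it passes at about the nominal 10% rate.

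**Step 4: type I error.** Under the null each analysis alone rejected in about 5% of simulated trials. The unadjusted change and baseline-adjusted ANCOVA statistics have correlation √((1 + ρ)/2), that is 0.806, 0.866 and 0.922. The bivariate normal then gives a probability that at least one is significant of 7.8%, 7.3% and 6.8%. For the unadjusted and screened analyses, the simulation gave 7.9%, 6.8% and 6.7%.

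**The case against.** **ANCOVA looks like the intended method.** The section opens with it, the Sample size section refers to it, and the sequence can be read as steps towards the adjusted model. A reader might infer that the primary comparison is simply an unadjusted change score and that power is lost outright. The article does not support that. AUC-total is itself a listed covariate for the primary outcome, and if the adjusted model decides, the loss is 1 to 2 points. The larger losses are conditional on the unadjusted result deciding. This part of the objection stands.

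**The sample size does not depend on an ANCOVA gain.** A reader might infer that it does. The 60% is computed without one, and the text says only that power may be higher. This stands.

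**No rule says that either result suffices.** The 7 to 8% error is a worst case, not something the protocol prescribes. The code also stays unbroken until conclusions are drawn, which limits choosing by direction of effect. It does not prevent choosing the smaller p-value, since a two-sided p-value is visible with coded arms. The objection stands in part.

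**Dropping the strata is conservative.** It usually widens standard errors, and covariates only weakly related to the outcome cost little when omitted. This stands and limits the severity.

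**The deciding model may be named elsewhere.** The article refers to a pre-established analysis plan that is not shown. The missing precedence rule is therefore weak as a point by itself. The p<0.1 screen, however, is written into the protocol: a plan that follows it inherits the problem, and one that does not contradicts it.

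**Conclusion.** The point holds as a defect in a stated rule, at a severity below a mandatory correction. The protocol screens covariates for the primary outcome on p<0.1, protects neither entry AUC-total nor the strata from that screen, and leaves undesignated which of two results decides.

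The unadjusted change score, if decisive, costs about 17, 12 and 6 points of power against baseline-adjusted ANCOVA at ρ of 0.3, 0.5 and 0.7 (62.8 − 45.4, 71.1 − 58.7 and 86.3 − 80.4 before rounding). The screened model, if decisive, costs little power but usually omits the strata when these act on level rather than change.

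These sizes rest on assumed values of ρ, equal SDs at both visits, a two-sided test, 40 complete participants per arm, reading the AUC-total row of Table 1 as the entry value, and assumed covariate effects in the simulation. Nothing here shows the stated 60% to be wrong, or that either analysis alone has an inflated error rate.

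**What to change.** In the Statistical methods section, delete the p<0.1 screen for the primary outcome and name one deciding model: ANCOVA of AUC-total on arm, entry AUC-total, age stratum (18–31/32–60) and sex, all always included. Label the AUC-total row of Table 1 as the entry value.

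The change score can stay as the dependent variable. If (week 4 − entry) = a + b·arm + c·entry, then week 4 = a + b·arm + (c + 1)·entry, so the treatment estimate b and its test are the same; adding age stratum and sex does not alter this.

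Apply the existing MI-over-complete-case rule to that one model. Report the unadjusted change, and any model adding body mass index, smoking and entry HAMD, as sensitivity analyses.

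The cost is wording only. Every variable is already collected, enrolment was still open at the reported status, and the randomization code is not to be broken until analysis is finished. The change should be dated before the code is broken and before any outcome analysis.

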### Blinding

All study personnel and participants are blinded to the packaging of the study drug, and blinding is maintained throughout monitoring, follow-up, data management, assessment of outcomes and data analyses. The randomization code will not be broken until all the data has been analysed and conclusions drawn. At the assessment after four weeks intervention, every participant, the sponsor-investigator (UK), and the neuropsychological testers will make a guess as to which intervention the participant has received. When the trial is finished, inter-rater reliability between the actual intervention and the guesses will be estimated to assess the degree to which blinding has been successful.

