### Data management

All the data of each participant is kept in a Case Record File, which fulfils the Danish law for medical doctors' obligation to keep patient records. In order to maintain blinding, the result of serum escitalopram concentration at end of the intervention is sent to the CTU, that keeps it in a locked safety box until the practical part and the data analyses of the trial are finished. Participants are not registered in The Danish Psychiatric Central Research Register or in any local hospital registers.

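### Table 1 lists end-of-treatment drug level as a covariate for every outcome; the later drug-level model is not valid as specified, although the main treatment comparison is unaffected

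*Protocol article*

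**What the plan says.** All references are to the protocol article.

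- **Statistical methods, Table 1**, captioned "Covariates in the statistical models for the AGENDA trial", marks drug level for the primary outcome, neuroticism, cognitive function and the tertiary outcomes. It stands in the same list as age, gender and entry body mass index. Nothing marks it as exploratory, as a later step, or as limited to one arm.
- **Statistical methods, text.** Outcomes are analysed "firstly unadjusted and then adjusted for a number of variables, if they present with a p-value < 0.1 in the univariate analyses". On drug level the plan is staged: "Initially the drug level measured in each participant will not be included in the models in order as to keep the analysers blinded". Then: "Later on analyses for the effect of drug-level will be performed along with other significant covariates in the multivariate model".
- **Data management** shows what the variable is: "the result of serum escitalopram concentration at end of the intervention is sent to the CTU". The values stay locked away until the data analyses are finished.
- **Blinding**: "The randomization code will not be broken until all the data has been analysed and conclusions drawn".
- The main null hypothesis is that "there is no difference between the two intervention arms with regard to the plasma cortisol AUC-total in the DEX-CRH test".

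**The concern.** Adjusting a randomised comparison is safe when the covariates are fixed before treatment starts. Drug level is not: it is produced by the allocation. The article does not say that it is zero on placebo, but withholding it to protect blinding concedes that it discloses the arm. The only reason given for leaving it out at first is blinding, not validity, so once that reason lapses the plan puts it in with the other covariates.

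The text does not say whether arm stays in that later model. Either choice gives a coefficient that is easy to misread. With arm kept, the arm coefficient compares treated and untreated people at the same drug level, which extrapolates the escitalopram arm to a level of zero. With arm dropped and both arms pooled, the apparent drug-level effect mostly restates the difference between arms. At stake is the reading of a follow-up analysis planned for every outcome.

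**Working it through.** **Inputs from the document.** Difference: "the relevant difference we aim to detect or reject is 15,064 – 7,773 = 7,291 nmol × min/L" (Sample size). SD 14,768 (Sample size). 80 participants, 1:1 allocation, so 40 per arm (Sample size, Randomization). Significance level 0.05, taken as two-sided.

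**Assumptions.** The document gives no spread of concentrations. I take the level as 0 on placebo and, on escitalopram, with coefficient of variation c = 0.3, 0.5 or 0.8.

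**Step 1: the plan's own figure, without drug level.** SE = 14,768 × √(2/40) = 3,302. Then 7,291 / 3,302 = 2.208, and power = Φ(2.208 − 1.960) = 0.598. The stated 60% is reproduced. It belongs to a comparison that excludes drug level.

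**Step 2: overlap of level with arm.** With mean level μ on escitalopram, the between-arm variance is μ²/4 and the average within-arm variance is c²μ²/2. The between-arm share is therefore 1/(1 + 2c²), which is also the squared correlation of level with arm. The variance inflation factor (VIF) for arm is (1 + 2c²)/(2c²).

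| c | Between-arm share | Correlation | VIF | SE multiplier |
|---|---|---|---|---|
| 0.3 | 1/1.18 = 0.85 | 0.92 | 1.18/0.18 = 6.6 | 2.6 |
| 0.5 | 1/1.50 = 0.67 | 0.82 | 1.50/0.50 = 3.0 | 1.7 |
| 0.8 | 1/2.28 = 0.44 | 0.66 | 2.28/1.28 = 1.8 | 1.3 |

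**Step 3: simulation.** 4,000 trials per setting, 40 per arm, log-normal levels with mean 1, true average effect −7,291. Arm-only power was 57% to 60% throughout.

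*Arm and level in one model, read on arm:*

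| c | Effect proportional to level: mean arm coefficient, % significant | Effect independent of level: % significant |
|---|---|---|
| 0.3 | −31, 4.9% | 13.7% |
| 0.5 | 37, 4.3% | 23.5% |
| 0.8 | −160, 5.3% | 35.7% |

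When the drug works through its concentration, the arm coefficient is about 0 although the treatment effect is real. That change of meaning does not depend on c.

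*Level only, both arms pooled, true effect independent of level:* the drug-level coefficient was −6,334, −4,954 and −3,539 per mean level, and significant in 53%, 42% and 30% of trials at c = 0.3, 0.5 and 0.8. No exposure-response relation existed among treated participants, so these findings come from the arm contrast alone.

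**Step 4: where exposure-response information lies.** Placebo values are constant at 0. With arm in the model, the drug-level slope is therefore estimated entirely from the spread within the escitalopram arm. Only about 40 participants inform it, whichever valid model is used.

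**The case against.** The strongest reply is that the plan already protects the main result. The unadjusted and initial adjusted comparisons exclude drug level, the concentrations stay locked until the analyses are done, and conclusions come before the code is broken. No passage makes the later model primary or lets it replace the others. Where the plan wants one analysis to prevail, as with multiple imputation over complete cases, it says so. All of this stands. A reader might infer from Table 1 that the trial's adjusted treatment effect becomes uninterpretable, or that a valid randomised result could be overturned. The documents do not support that.

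The later model is also aimed at the effect of drug level, not at an arm effect adjusted for it, and the text does not say that arm is kept. That is fair, and the loss of power for arm in step 3 applies only if arm is kept. But dropping arm does not rescue the model, because pooled placebo zeros then drive the coefficient.

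Calling level and arm nearly collinear also goes too far in general: the correlation is 0.92 at c = 0.3 but 0.66 at c = 0.8, and the document gives no c.

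Finally, details of a follow-up model may sit in the analysis plan that the article mentions. The covariate list, however, is fixed in the article itself, and as printed it treats an on-treatment concentration like a baseline variable.

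**Conclusion.** The point holds in a limited form. The test of the main null hypothesis and its roughly 60% power are untouched. The later drug-level model, as specified for all outcomes, is not valid on either reading:

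- **Arm kept:** the arm coefficient is a contrast at equal drug level, not a treatment effect, and its SE is about 1.3 to 2.6 times larger.
- **Arm dropped:** the drug-level coefficient is largely the arm contrast, with about 44% to 85% of the variance in level lying between arms.

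The ranges rest on assumed coefficients of variation of 0.8 to 0.3 and on levels of zero on placebo, a reasonable inference that the text does not state. The qualitative conclusion needs only that level is a consequence of allocation.

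**What to change.** 1. Remove drug level from the Table 1 covariates for treatment comparisons.
2. State that treatment effects for all outcomes come only from models without drug level.
3. Replace the sentence on later analyses with an exploratory exposure-response regression within the escitalopram arm, adjusted for baseline covariates (for example entry AUC-total, age and sex) and reported as non-randomised.

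The cost is one table row and a sentence or two, with no new data. The downside is lower precision, because only about 40 participants contribute. Per mean level, the slope's SE is roughly 14,768/(c√40), or about 7,800, 4,700 and 2,900 at c = 0.3, 0.5 and 0.8. The simulated pooled level-only model gave about 3,050, 2,750 and 2,340. That apparent gain comes from the arm contrast, so no exposure-response information is lost.

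Optionally, label the AUC-total row in Table 1 as the entry value, as is done for HAMD and body mass index. The entry value is already the natural reading, so this is only a clarification.
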